#### Descriptive data

At baseline, patient’s age, height, weight, and sex will be collected for descriptive purposes. The patient’s weight will be categorized into underweight (BMI < 17 kg/m^2^), normal weight (17 ≤ BMI < 25 kg/m^2^), overweight (25 ≤ BMI < 30 kg/m^2^), and obese (BMI ≥ 30 kg/m^2^) by applying the patients’ BMI adjusted for age [30]. The patient’s position during the study LP procedures and the level of anesthesia will be registered. Also, the provider’s experience in performing LP procedures will be requested and divided into three categories (< 10, 11–100, and > 100 LPs performed before the study).

### Data collection and management

The data collection of each study LP procedure will take place at different time points: immediately after performing the procedure, after a week, and after the 4-week follow-up, as described above.

As the participant may undergo up to four study LP procedures during the study, color-coded CRFs will be prepared for each procedure and compiled into the Participant File of the given patient. Pseudonymized copies of the Participant Files will be regularly delivered to the sponsor for data analysis, but no interim analyses are preplanned. However, reported safety data on symptoms, complications, and adverse events will be regularly checked to ensure that safety or vigilance issues requiring further actions will be detected in time.

In case of a device-related serious adverse event with at least a probable link to the use of IQ-Tip system, the local investigator (i.e., the provider of the given LP procedure), the principal investigator, and the sponsor representatives will discuss the incident and decide within 3 days whether the enrolment of participants and the trial need to be suspended. If the suspension is attributed to the medical device, National Competent Authority will be informed.

If the issues underlying the trial suspension cannot be resolved within a reasonable timeframe and potential safety issue persists, the trial may be prematurely terminated upon the decision of the principal investigator and the sponsor. Ethics committee and National Competent Authority will be informed about premature termination. Suspension or premature termination of the trial does not affect the participants’ treatment and care.

During the study LP procedures of the study arm A, the raw bioimpedance measurement data will be collected into the analyzer memory, wherefrom the data will be regularly transferred to a computer and backed-up on an external memory. Participant’s identity cannot be recognized from the raw data, but if deemed necessary, the data can be traced to an individual participant’s identity using the time and date information stored along with the raw bioimpedance data and the original Participant’s File.

Original Participant Files and signed informed consent forms will be archived at the collaborating university hospitals for 15 years.

### Monitoring

The principal investigator [name] and the sponsor representatives ([name]) comprise a team which is responsible for daily conduct and progress of the trial throughout the study parallel with the formal monitoring. The monitoring plan (date 30/09/2022) dictates the principles of how the conduct of the trial at the investigational sites will be audited. The sponsor will be responsible for monitoring.

Besides the site initiation visits before the start and the site close-out visits after the last LP procedure of the study, at least two monitoring visits to each investigational site are planned, the first within about 2 months after the first study procedure and the second one about a few months before the last anticipated procedure.

The focus of the site monitoring and the close-out visits will be on the following issues.Informed consent is properly obtained from each participant.Processes for individual data protection are obeyed.Study LP procedures are performed in the allocated order using the proper spinal needle.Investigators are familiar with the guidance about reporting potential adverse events, serious adverse events, and device deficiencies to the sponsor.The original CRFs are properly filled and signed.The CRF copies delivered to the sponsor match the original CRFs.

Accuracy of data transferred from the symptom diaries and electronic health records to the CRFs will be verified by random sampling of three CRFs filled during the preceding two months. Violations of the protocol will be registered and managed as appropriate.

### Data analysis

Mean, standard deviation (SD), median, interquartile range (IQR), range, and proportions will be used as the main descriptive statistics as appropriate for the data. A cumulative distribution curve will be used as the main descriptive statistics for erythrocyte count data in CSF [14]. This curve illustrates the respective proportions of CSF samples, which denote the incidence of TLP for any given criterion of the erythrocyte count. For the chosen criterion, the incidence of TLP is the vertical distance (in %) from the corresponding curve point up to the 100% point.

The sample size was estimated by an online power calculator for a binary outcome in a non-inferiority trial [31]. For the estimation, it was assumed that the incidence of TLP with the IQ-Tip needle system (study arm A) is 20% and 30% with the conventional spinal needle (study arm B). The values are based on our data on the IQ-Tip system [19] and conventional needle [14] in pediatric hemato-oncology patients, respectively. Considering the 5% noninferiority margin, about 150 LP procedures in both arms will be needed to achieve 90% statistical power to demonstrate noninferiority at the significance level of *p* < 0.05. Assuming a total of 26 TLPs out of 150 procedures in the arm A, corresponding to the 17.3% incidence of TLP in our previous study [19], the total number of TLPs in the arm B should be at least 30 (20%) to demonstrate noninferiority, and at least 40 (26.7%) to demonstrate superiority for the IQ-Tip system. These relationships are illustrated in Fig. 2.

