**Fig. 2 Fig2:**
[figure not shown]
Schematic on the relation between the numbers of traumatic LP procedures (TLP) with the IQ-Tip system and conventional spinal needle required to indicate noninferiority (green area) or not (red area)

The primary statistical comparison of outcome variables will be based on the true use of the allocated spinal needles in the study LP procedures. Therefore, per-protocol analysis will be employed in the efficacy analysis as recommended for noninferiority trials [32]. The incidences of TLP and PDPH as well as the first puncture success rate between the respective study arms will be compared with the Chi-squared test. The 95% confidence intervals (95% CI) for the difference will be calculated using the exact Clopper-Pearson method. Between-arm comparisons of blood and CSF data, other performance parameters, and incidences of other complications will be performed for descriptive purposes. Definitions of the outcome variables to be used in the efficacy analysis are presented in Table 2 in terms of domain, measurement, metric, aggregation, and time point according to a recommended framework for clinical trials [33, 34]. In case of missing data, data estimation nor imputation will not be performed.

**Table 2 Tab2:** Definitions of the outcome variables (only those domains pertinent to the efficacy analysis are presented) in terms of domain, measurement, metric, aggregation, and time point

Domain	Specific measurement	Metric	Method of aggregation	Time point
Incidence of TLP	Flow cytometry	Erythrocyte count ≥ 10/µL (yes/no)	Proportion	Each study LP procedure
First puncture success rate	Provider’s self-report on CRF	Occurrence (yes/no)	Proportion	Each study LP procedure
Incidence of PDPH	Symptom diary	Occurrence (yes/no)	Proportion	Within 1 week after each study LP procedure
Peripheral blood analysis	Flow cytometry	Erythrocyte count (cells/µL) Hematocrit (%) Hemoglobin (g/L) Leukocyte count (cells/µL) Thrombocyte count (cells/µL) Existence of blasts (yes/no)	Mean Mean Mean Mean Mean Proportion	Each study LP procedure
CSF analysis	Flow cytometry	Erythrocyte count (cells/µL) Leukocyte count (cells/µL) Existence of blasts (yes/no)	Cumulative distribution curve Mean Proportion	Each study LP procedure
Number of LP attempts	Provider’s self-report on CRF	Number	Median	Each study LP procedure
Number of failed procedures	Provider’s self-report on CRF	Occurrence (yes/no)	Proportion	Each study LP procedure

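### The 90% power and the noninferiority count of 30 rest on an unstated one-sided 5% level that conflicts with the planned 95% CI, and the superiority count of 40 misses the planned chi-squared test

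*Protocol article*

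**What the plan says.** The sample size paragraph under Data analysis in the protocol article makes this assumption: "the incidence of TLP with the IQ-Tip needle system (study arm A) is 20% and 30% with the conventional spinal needle (study arm B"). It goes on: "Considering the 5% noninferiority margin", and gives the requirement as "about 150 LP procedures in both arms will be needed to achieve 90% statistical power". The goal of that power is put as "to demonstrate noninferiority at the significance level of *p* < 0.05". Whether that level is one-sided or two-sided is not said.

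The same paragraph then gives a worked example. "Assuming a total of 26 TLPs out of 150 procedures in the arm A" (17.3%), it says that "the total number of TLPs in the arm B should be at least 30 (20%) to demonstrate noninferiority, and at least 40 (26.7"%), the second count being the one for superiority. Figure 2 is cited as showing these relationships.

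Further on under Data analysis, after Figure 2, the TLP incidences are to be compared with a chi-squared test, and "The 95% confidence intervals (95% CI) for the difference will be calculated" by a named exact method. No 90% interval and no one-sided level appears anywhere in the article. The end of the Background makes superiority on TLP part of the primary objective, alongside noninferiority.

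**The concern.** Power, decision counts, test and interval should all come from the same error level, or from levels that are declared separately. Here one unqualified significance level is followed by two counts that no single level produces, and by an interval at a confidence level that matches neither the stated power nor the first count.

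The stake is the primary claim. With 26 versus 30 or 31 TLPs, the sample size paragraph calls the device noninferior while the 95% interval in the results would cross the margin. With 26 versus 40 it calls the device superior while the planned test is not significant. Choosing between 90% and 95% limits once the data are known would be a choice between a nominal 5% and 2.5% risk of a false noninferiority claim. The sponsor makes the device, so that choice should be closed in advance.

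**Working it through.** **Inputs (Data analysis).** Design incidences 0.20 (A) and 0.30 (B); margin 0.05, taken as an absolute difference because that reproduces the stated figures; 150 procedures per arm; power 90%; example count 26/150 in A; stated counts of 30 and 40 in B. Procedures are treated as independent, as the stated calculation does.

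**1. Sample size and power**

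n per arm = (z_α + z_β)² × [0.20×0.80 + 0.30×0.70] / (0.10 + 0.05)², where the bracket is 0.37 and the denominator 0.0225.

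- One-sided 5%: (1.645 + 1.282)² × 0.37/0.0225 = 140.8, so 141 per arm.
- One-sided 2.5% (two-sided 95% CI): (1.960 + 1.282)² × 0.37/0.0225 = 172.8, so 173 per arm, or 346 procedures.

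Power at 150 = Φ(0.15/√(0.37/150) − z_α) = Φ(3.020 − z_α).

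- One-sided 5%: Φ(1.375) = 91.5%. This reproduces the stated 90%.
- One-sided 2.5%: Φ(1.060) = 85.5%.

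Exact binomial enumeration of the same decision rule gives 91.5% and 85.5%.

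**2. Noninferiority count**

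Upper limit of A − B = d + z × √[p_A(1−p_A)/150 + p_B(1−p_B)/150], with p_A = 26/150. For 30 in arm B, d = −2.67 points and the standard error is 4.50 points. In percentage points:

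| TLPs in B | Upper limit, 90% CI | Upper limit, 95% CI |
|---|---|---|
| 29 | 5.35 | 6.75 |
| 30 | 4.73 | 6.15 |
| 31 | 4.11 | 5.54 |
| 32 | 3.49 | 4.93 |

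So 30 is exactly the first count that passes with a 90% CI. With a 95% CI the first is 32. Other interval methods agree: at 30 the 95% limit is 6.19 (Newcombe) or 6.21 (Miettinen-Nurminen), and at 32 it is 4.98 or 4.99.

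**3. Superiority count**

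Pearson chi-squared for 26/150 versus 40/150: the pooled proportion is 66/300 = 0.22, so z = 0.0933/√(0.22×0.78×2/150) = 1.951, χ² = 3.807 and p = 0.0510.

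| TLPs in B | Pearson p | Yates p | Fisher p | Upper limit, 95% CI (unpooled Wald) |
|---|---|---|---|---|
| 40 | 0.0510 | 0.070 | 0.070 | −0.02 |
| 41 | 0.0376 | 0.052 | 0.052 | −0.64 |
| 42 | 0.0274 | 0.039 | 0.038 | −1.27 |

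The count of 40 is where an unpooled Wald 95% limit first falls below zero, so it probably came from such an interval. At the level behind the 30 (one-sided 5%), superiority would already be reached at 38 (90% CI upper limit −0.26; 37 gives +0.37). The 30 and the 40 therefore rest on different error levels.

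**The case against.** The best defence is that a noninferiority test is one-sided by nature and that 5% is a legitimate level. On that reading the sample size is right, with 91.5% power at 150 per arm and a planned total that is only a minimum. The article also never says that the 95% CI decides noninferiority. The same interval is attached to secondary outcomes without formal hypotheses, so it may be ordinary reporting. One-sided 5% for noninferiority with two-sided 5% for superiority is a coherent pair, the counts are a worked example for one assumed arm A result, and 40 misses the chi-squared test by very little.

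Much of this is fair. One-sided 5% is not an error in itself, the superiority discrepancy is one event wide, and no trial conduct depends on 30 or 40. But the level and the pairing would have to be stated, and they are not. The 95% CI is the only interval named and the only planned output that can address a 5-point margin, since a chi-squared test of equality cannot. The counts are worded as minimum requirements for each claim.

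It can also be said that the limits above do not use the interval method the article names. Clopper-Pearson is a method for a single proportion and does not by itself define a limit for a difference. The three standard methods for a difference used above agree on 32.

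**Conclusion.** The concern holds. The stated 90% power and the count of 30 are correct only at one-sided 5%. Against the planned 95% interval, power is 85.5%, a shortfall of 4.5 points, and the noninferiority count is two too low (32, not 30). The superiority count rests on a different level from the noninferiority count and is one too low for the planned Pearson test (41, not 40), or two too low with Yates' correction or Fisher's test (42).

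This assumes an absolute margin, 150 independent procedures per arm, and the 95% interval as the basis for judging noninferiority. The last is an inference, but the article offers no other basis. Correlation between procedures in the same patient is outside both the stated figures and these.

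**What to change.** State the error level, the interval and the decision rule for noninferiority, and derive power and both counts from them.

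- **Preferred:** one-sided 2.5%, that is, the upper limit of the two-sided 95% CI below 5 points. Restate power at 300 procedures as about 86% under 20% versus 30%. For 26 TLPs in arm A, restate the arm B counts as 32 (21.3%) for noninferiority and 41 (27.3%) for superiority by the uncorrected chi-squared test.
- **Alternative:** if one-sided 5% is intended, say so and report a 90% CI for the noninferiority decision. The 90% power and the count of 30 then stand. Superiority should be declared as tested at two-sided 5%, and its count still changes to 41.

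In either case, say whether the chi-squared test is continuity-corrected, and redraw Figure 2 to match whichever counts are kept. The figure is not shown here, so its boundaries need checking against the chosen rule.

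The cost is revised text and one figure. No patients or procedures are added. Under the preferred option the stated power becomes slightly less favourable; restoring 90% would take 173 procedures per arm, but the fix does not require it.

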**Fig. 2 Fig2:**
[figure not shown]
Schematic on the relation between the numbers of traumatic LP procedures (TLP) with the IQ-Tip system and conventional spinal needle required to indicate noninferiority (green area) or not (red area)

The primary statistical comparison of outcome variables will be based on the true use of the allocated spinal needles in the study LP procedures. Therefore, per-protocol analysis will be employed in the efficacy analysis as recommended for noninferiority trials [32]. The incidences of TLP and PDPH as well as the first puncture success rate between the respective study arms will be compared with the Chi-squared test. The 95% confidence intervals (95% CI) for the difference will be calculated using the exact Clopper-Pearson method. Between-arm comparisons of blood and CSF data, other performance parameters, and incidences of other complications will be performed for descriptive purposes. Definitions of the outcome variables to be used in the efficacy analysis are presented in Table 2 in terms of domain, measurement, metric, aggregation, and time point according to a recommended framework for clinical trials [33, 34]. In case of missing data, data estimation nor imputation will not be performed.

**Table 2 Tab2:** Definitions of the outcome variables (only those domains pertinent to the efficacy analysis are presented) in terms of domain, measurement, metric, aggregation, and time point

Domain	Specific measurement	Metric	Method of aggregation	Time point
Incidence of TLP	Flow cytometry	Erythrocyte count ≥ 10/µL (yes/no)	Proportion	Each study LP procedure
First puncture success rate	Provider’s self-report on CRF	Occurrence (yes/no)	Proportion	Each study LP procedure
Incidence of PDPH	Symptom diary	Occurrence (yes/no)	Proportion	Within 1 week after each study LP procedure
Peripheral blood analysis	Flow cytometry	Erythrocyte count (cells/µL) Hematocrit (%) Hemoglobin (g/L) Leukocyte count (cells/µL) Thrombocyte count (cells/µL) Existence of blasts (yes/no)	Mean Mean Mean Mean Mean Proportion	Each study LP procedure
CSF analysis	Flow cytometry	Erythrocyte count (cells/µL) Leukocyte count (cells/µL) Existence of blasts (yes/no)	Cumulative distribution curve Mean Proportion	Each study LP procedure
Number of LP attempts	Provider’s self-report on CRF	Number	Median	Each study LP procedure
Number of failed procedures	Provider’s self-report on CRF	Occurrence (yes/no)	Proportion	Each study LP procedure
Incidence of symptoms, complications, and adverse events	Search from hospital electronic health records	Occurrence (yes/no)	Proportion	Within four weeks after each study LP procedure

As an exploratory analysis, logistic regression analysis will be performed to assess factors that may account for the incidence of TLP, defined as a dichotomous variable (yes/no) by the criterion of ≥ 10 erythrocytes/μL. The TLP values will be obtained from the patients’ 2nd, 3rd, and 4th study LP procedures. The following dichotomous variables (yes/no) will be entered to the model as predictors: whether the preceding procedure was performed with a conventional spinal needle, whether the preceding procedure was TLP, whether the consecutive procedures were performed within a week (≤ 7 days) or two (≤ 14 days), whether the patient was obese (BMI ≥ 30 kg/m^2^), whether the provider was experienced with more than 100 previous LP procedures, and whether the thrombocyte count was less than 50,000 platelets/μL [11, 12, 14, 19]. Estimated odds ratios (OR) of the entered predictors will be reported with 95% CIs. The robustness of predictors and related ORs will be verified by performing both backward and forward regression analyses.

Statistical analyses will be done with a concurrent version of IBM SPSS Statistics for Windows (IBM Corp., Armonk, NY, USA).

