**Methods:**

The study is a multicenter, randomized, two-arm crossover noninferiority trial of pediatric hemato-oncology patients that will be conducted within the usual clinical workflow. Patients’ LP procedures will be performed alternately either with the IQ-Tip system (study arm A) or a conventional Quincke-type 22G spinal needle (study arm B). For each enrolled patient, the order of procedures is randomly assigned either as ABAB or BABA. The total number of LP procedures will be at least 300, and the number of procedures per patient between two and four. After each study LP procedure, the performance will be recorded immediately, and 1-week diary-based and 4-week record-based follow-ups on symptoms, complications, and adverse events will be conducted thereafter. The main outcomes are the incidence of traumatic LP, first puncture success rate, and incidence of post-dural puncture headache.

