## Materials and methods

### Trial design and setting

The present study (acronym IQ-LP-04) is a multicenter, randomized, two-arm crossover noninferiority trial of pediatric hemato-oncology patients. Since the patients act as their controls in the cross-over design, the potential bias due to variability between the patient characteristics is effectively controlled for. The two study arms refer to performing the patient’s LP procedures alternately using the IQ-Tip system (study arm A) or a conventional spinal needle (study arm B). The arm of the first study procedure will be randomly assigned, while the number of procedures per patient will be between two and four. Thus, the two possible randomly assigned sequences of the study LP procedures are ABAB and BABA.

All study LP procedures are part of patients’ preplanned LP procedures without additional procedures or laboratory tests. Only the data needed for the management of patients’ malignant diseases will be collected as part of routine therapy and evaluation, independent of the present trial. Biological specimens for genetic or molecular analyses will not be collected. If the patient’s treatment or medical condition requires concomitant care, modification, or other interventions during the study, they will be permitted. The crucial point for the study is that the allocated spinal needles are used in the study LP procedures as intended. Patients’ treatments and care will continue as planned after completing the trial or withdrawing from the study due to any reason. There are no specific plans for promoting participant retention during the study. The pragmatic nature of the present trial is expected to promote complete follow-up and acquisition of data.

After each study LP procedure, there will be a 1-week follow-up using a symptom diary and a 4-week follow-up of hospital electronic health records. The flow chart of the study LP procedures is shown in Fig. 1, whereas the schedule of enrolment, study LP procedures, and assessments during the post-allocation period are outlined in Table 1. This protocol has been written according to the SPIRIT reporting guidelines [27] and verified against the SPIRIT checklist.

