### Randomization and allocation

The spinal needle that will be used in the patient’s first study LP procedure, either the IQ-Tip system (study arm A) or a conventional spinal needle (study arm B), was determined by block randomization before recruiting patients. Block randomization ensures an approximately even number of both sequences of study LP procedures (ABAB and BABA) in random order while eliminating the bias that may arise from a fixed order of LP procedures.

With a dedicated Matlab script, the sponsor has generated randomization lists for each investigational site beforehand (date 30/09/2022). The sponsor will also prepare and deliver enough sequentially numbered sealed envelopes containing the randomly assigned sequences (either ABAB or BABA) to the investigational sites. During the trial, the person who will perform the statistical analyses will not meet the participants nor be involved anyhow in collecting data or filling their case report forms (CRF).

Upon enrolling a new patient to the study, the next available envelope in the order will be opened to reveal the sequence of study LP procedures for the given patient. This sequence determines the choice of a specific Participant’s File, a binder that contains color-coded CRFs and other relevant documents for collecting the data from the four study LP procedures. The running number of the envelope together with the hospital-specific three-letter prefix will determine the patient’s pseudonym (ID code).

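### The primary test treats a crossover of 2 to 4 alternating procedures per patient as two independent groups, so its standard error does not fit the design; the error is conservative and costs efficiency, mainly for superiority

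*Protocol article*

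**What the plan says.** - **Design.** The abstract states: "The total number of LP procedures will be at least 300, and the number of procedures per patient between two and four". Under Trial design and setting, "the two possible randomly assigned sequences of the study LP procedures are ABAB and BABA", so every patient with at least two procedures contributes to both arms. The stated reason for the design begins: "Since the patients act as their controls in the cross-over design".
- **Randomisation.** Patients are allocated individually from block lists. Under Randomization and allocation, "the sponsor has generated randomization lists for each investigational site beforehand", which makes site a stratum.
- **Primary and secondary comparisons.** Under Data analysis, the two incidences and the success rate "between the respective study arms will be compared with the Chi-squared test". The next sentence adds: "The 95% confidence intervals (95% CI) for the difference will be calculated using the exact Clopper-Pearson method". The Outcomes section uses the number of procedures as the denominator in each arm.
- **Sample size.** Data analysis assumes 20% traumatic punctures with IQ-Tip and 30% with the conventional needle, a 5% margin, p < 0.05 and 90% power. An online calculator for a binary noninferiority outcome gives about 150 procedures per arm.
- **Objective.** The end of the Background sets the primary objective as noninferiority, or noninferiority together with superiority, on traumatic puncture.
- **Only regression in the plan.** An exploratory logistic model uses procedures 2 to 4. It does not estimate the overall needle contrast and states no patient effect.

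**The concern.** A Chi-squared test on two arm totals assumes that all procedures are independent and that the arms hold different patients. Here the same patients are in both arms, and some appear twice within an arm. The article fixes this test itself, so a later analysis plan would have to override the text and not merely complete it.

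The plan also gives reason to expect dependence. Its exploratory model uses a traumatic preceding puncture, obesity and low thrombocyte count as predictors, and these are wholly or partly patient traits.

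At stake is whether the primary confidence interval has its stated coverage, and whether the precision that a crossover offers reaches the inference.

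**Working it through.** **Inputs from the protocol:** pA = 0.20, pB = 0.30, margin 0.05, 150 procedures per arm, 2 to 4 procedures per patient. **Assumed:** a common within-patient correlation ρ of 0.1 to 0.4, since the documents give none. Sidedness is not stated either, so both levels are tried below.

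**1. Reproduce the plan's figure with independent groups.**

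- Variance term: 0.20×0.80 + 0.30×0.70 = 0.37.
- n per arm = 0.37 × (1.645 + 1.282)² / (0.05 + 0.10)² = 141, or about 154 with a continuity correction.
- SE at 150 per arm = √(0.37/150) = 0.0497. Power = Φ(0.15/0.0497 − 1.645) = 91.6%.
- At one-sided 0.025, n = 173 and power at 150 is 85.6%, which does not match the plan.
- The plan's example of 26 against 30 events also follows the independent formula. The difference is −0.0267 with SE 0.0450, so the one-sided 95% upper bound is −0.0267 + 1.645×0.0450 = 0.047, below 0.05. With 29 events the bound is 0.054.

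The sizing is therefore an independent-groups calculation at one-sided 0.05.

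**2. Standard error under the actual design.** Write sA = √0.16 = 0.400 and sB = √0.21 = 0.458. The variance of the difference is V/150, with:

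- 2 per patient: V = 0.37 − 2ρ·sA·sB
- 4 per patient: V = 0.37(1 + ρ) − 4ρ·sA·sB
- 3 per patient (half ABA, half BAB): V = 0.37(1 + 2ρ/3) − (8/3)ρ·sA·sB

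Example, ρ = 0.2 and two per patient: V = 0.37 − 0.0733 = 0.2967, so SE = 0.0445.

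| ρ | True SE, 2 or 4 per patient | Unpaired SE too large by | True SE, 3 per patient | Unpaired SE too large by |
|---|---|---|---|---|
| 0.1 | 0.047 | 5% | 0.048 | 3% |
| 0.2 | 0.0445 | 12% | 0.046 | 7% |
| 0.3 | 0.042 | 19% | 0.0445 | 12% |
| 0.4 | 0.039 | 29% | 0.043 | 16% |

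**3. Error rate at the margin.** Simulation of 35% against 30%, nominal one-sided 5%, 8,000 runs per setting. The unpaired analysis declares noninferiority in 4.2-4.5% of runs at ρ about 0.12, 3.0-3.3% at about 0.25 and 1.8-3.2% at about 0.39. A patient-clustered SE gives 4.8-5.7% over the same settings.

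**4. Noninferiority power, 20% against 30%, one-sided 0.05.** In the same simulations the planned analysis has 92.5-93.0% power at ρ about 0.10, 93.3-94.7% at about 0.21 and 94.8-96.2% at about 0.35. With the clustered SE the figures are 93.3-94.4%, 95.1-96.8% and 96.9-98.7%.

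**5. Superiority power at ρ = 0.2, two-sided 95% interval.**

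- Planned SE: Φ((0.10 − 1.96×0.0497)/0.0445) = about 52%.
- Correct SE: Φ(0.10/0.0445 − 1.96) = about 61% with 2 or 4 procedures, and Φ(0.10/0.0463 − 1.96) = about 58% with 3.
- A separate simulation with a patient random effect gives 52-53% against 60%.

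**The case against.** The strongest reply is that the error lies on the safe side. With alternating needles and positive correlation, a noninferiority claim from the planned test remains valid. The stated 90% power is met with the unpaired SE, and the trial is not powered for superiority. The correlation is undocumented, and near zero the whole effect is small. All of this stands, and it limits the point to a mismatch between interval and design with a loss of efficiency.

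Four stronger readings are tempting, and the documents do not support them:

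- **False noninferiority is inflated.** The simulated rates at the margin are below nominal under positive correlation. The direction could reverse only if exclusions (single procedures may be left out, and the analysis is per protocol) left many patients with several procedures in one arm and none in the other. Then the correlation within an arm would have no offsetting covariance between arms. Nothing in the plan makes that likely.
- **Patient differences are left uncontrolled.** The design section speaks of bias. Patients with two or four procedures count equally in both arms. Patients with three are randomised between ABA and BAB, which adds noise but no bias. Only the standard error misses the benefit.
- **Sites were randomised.** The lists are per site, but the patient is the unit randomised. Site is a stratum, and the effect of leaving it out cannot be sized from the documents.
- **The trial is too small.** The sample size is on the generous side if ρ is positive.

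**Conclusion.** The point holds in this limited form. The planned test and the sample size both treat 300 procedures as independent units, which contradicts the crossover that the protocol describes and justifies. The point estimate is unaffected.

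Under an assumed common correlation of 0.1 to 0.4, the interval is about 3% to 29% wider than it should be. The practical cost is modest for noninferiority and larger for superiority, at about 8 percentage points of power when the correlation is 0.2. The mismatch between test and design is certain, because it is in the text. Its size depends on a correlation that the documents do not give. The noninferiority figures also assume the one-sided 0.05 level that reproduces the sample size, and the superiority figures a two-sided 95% interval.

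**What to change.** Replace the primary comparison with a patient-clustered risk difference: for example GEE with identity link, or a logistic model with marginal standardisation, and a cluster-robust standard error in either case. Include needle, procedure number (1 to 4) and site as the randomisation stratum. Judge the confidence bound of the needle effect against the 5% margin, and state the sidedness. Use the same approach for first puncture success and post-dural puncture headache, and keep the Chi-squared test as a descriptive check.

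A clustered variance also adapts if exclusions unbalance the arms within patients, which the planned test cannot do. Any other analysis that respects the patient pairing would cure the core defect; the site and procedure-number terms are a sensible addition. The sample size can stay, with a note that it assumes independence and is conservative under positive correlation.

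The cost is a change of wording and slightly more programming. Patient code, hospital prefix and sequence are already recorded. If the correlation turns out to be zero, little is lost: in simulation the clustered analysis then rejected at the margin in 4.9-5.6% of runs, against 5.1-5.5% for the unpaired one.
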